# OBJECTIVES

## Primary objectives:

The primary objective of the study is to measure the day 28, PCR-corrected cure ratios of dihydroartemisinin-piperaquine and artemether-lumefantrine and demonstrate that:

- The cure ratio of dihydroartemisinin-piperaquine is non-inferior to that of artemether-lumefantrine (non-inferiority margin = 5%);
- The cure ratio of dihydroartemisinin-piperaquine is at least 90%.

This cure ratio is defined as the proportion of evaluable patients with adequate clinical and parasitological response at day 28.

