## Study design

This study is part of a phase III, randomized, open label, two-armed study involving 5 study centres, which will enroll a total 1,500 patients (1,000 dihydroartemisinin-piperaquine; 500 artemether-lumefantrine). Each study will enroll 300 patients into the multicentre study protocol (the other study sites are in Mozambique, Burkina Faso, Uganda, Zambia). In addition, 200 additional patients will be enrolled in the KEMRI study (1) to allow an independent statistical analysis of the KEMRI study and (2) to increase the precision of the estimated chemoprophylactic effect of dihydroartemisinin-piperaquine. Patients enrolled in the KEMRI study will also be followed up for a longer period until day 84 (instead of day 42). These changes will in effect act as an amendment to the multicentre study protocol and will not interfere with the analysis of the multicentre protocol. The data from the first 300 patients (day 0 - day 42) will be fully compatible with the multicentre protocol.

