### Sample size calculation

The study is designed as a non-inferiority trial.

The opinion of physicians and experts in malaria treatment has been sought for defining the non-inferiority margin, and this has been set at 5%. In addition, the experts have agreed that, in order for the new treatment to be considered efficacious, its PCR-corrected cure ratio at day 28 should not be lower than 90%. Therefore, in the present trial, dihydroartemisinin-piperaquine will be considered efficacious if both the following conditions are met (see section 2.1):

(i) The PCR-corrected cure ratio at day 28 of dihydroartemisinin-piperaquine is not inferior to the cure rate of artemether-lumefantrine by 5% or more, and independently of the reference drug performance,

(ii) The cure rate of dihydroartemisinin-piperaquine is at least 90%.

In summary, for the non-inferiority analysis, the clinical and statistical specifications for the sample size computations are as follows:

- Primary end point = PCR-corrected cure ratio at day 28.
- Primary analysis = based on 97.5% one-sided confidence intervals for the difference in day 28 cure ratios.
- Alpha = 0.025 (one-sided).
- Power = 80%.
- Cure ratio at day 28 of artemether-lumefantrine = 95% (results from multicentre phase III trial of Coartem in children; [name] personal communication).
- Non-inferiority margin for the difference (test-reference) = -0.05%.
- Analysis will be per-protocol.

To demonstrate non-inferiority of Artekin compared to Coartem the study will require 235 patients per treatment group. To allow for an approximate 5% loss to follow-up rate, 250 patients per treatment group (500 patients in total) will be enrolled in the Kilifi study.

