### Randomisation

Patients will be randomly assigned to one of the two treatment arms (dihydroartemisinin-piperaquine or artemether-lumefantrine). Blinding in the randomization process will be attained by the use of sealed envelopes. A Standard Operating Procedure (SOP) will control the use of the sealed envelopes.

The randomization list (blocks of 9) will be generated by MDS Pharma Services, using the plan procedure of SAS.

Treatment allocation and administration of medications will be performed by the study nurse or by the investigator at the clinic or during a home visit.

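### The planned 250:250 split cannot come from a list in blocks of 9, which fits the 2:1 multicentre design instead; the Kilifi allocation ratio is not settled

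*Protocol*

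**What the plan says.** Three sections of the protocol bear on allocation.

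- **Sample size calculation:** "the study will require 235 patients per treatment group". After an allowance for about 5% loss, "250 patients per treatment group (500 patients in total) will be enrolled in the Kilifi study". This is 1:1.
- **Study design:** the parent trial is one "which will enroll a total 1,500 patients (1,000 dihydroartemisinin-piperaquine; 500 artemether-lumefantrine"), which is 2:1, with 300 patients per site. Kilifi adds 200 patients of its own. Of the patients shared with the parent trial it says: "The data from the first 300 patients (day 0 - day 42) will be fully compatible with the multicentre protocol".
- **Randomisation:** "The randomization list (blocks of 9) will be generated" by the contract research organisation. The section describes one list for two arms and gives no ratio.

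No section states a ratio for the extra 200 patients, a second list or a second block size. The primary end point analysis is a confidence interval for the difference in day-28 cure ratios and does not mention stratification.

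**The concern.** The protocol fixes both the arm sizes and the block size, and the two are incompatible. No complete block of 9 holds equal numbers of each treatment, so the list as described would not deliver 250 per group. The odd block size alone only rules out 1:1; a 5:4 split is arithmetically possible. Read with the 1,000:500 parent design, 2:1 is the natural interpretation and the only unequal ratio that the document supports.

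At stake are the size of the comparator arm, the power quoted for the independent Kilifi analysis, and possibly the form of that analysis. If the shared 300 patients follow one ratio and the extra 200 another, treatment becomes associated with enrolment period, and an unstratified difference would pick up any change in cure over time.

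**Working it through.** **Inputs.** From Sample size calculation: "Alpha = 0.025 (one-sided"), power 80%, "Cure ratio at day 28 of artemether-lumefantrine = 95"% and about 5% loss. From Primary objectives: "non-inferiority margin = 5"%, taken as 5 percentage points (Sample size calculation prints -0.05%, but the analysis section uses -0.05). The test-arm cure ratio is not stated. I assume 95%, equal to the comparator, so each arm has variance 0.95 × 0.05 = 0.0475.

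**Step 1. The plan's own figure.** For equal arms, n per group = (z_alpha + z_power)² × 2 × 0.0475 / 0.05².

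- One-sided 0.025: (1.960 + 0.842)² = 7.849; 7.849 × 0.095 / 0.0025 = 298.3, so 299 per group.
- One-sided 0.05: (1.645 + 0.842)² = 6.183; 6.183 × 0.095 / 0.0025 = 234.9, so 235 per group.

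The stated 235 therefore matches one-sided 0.05, not the stated 0.025. It would also arise at 0.025 with an unstated test-arm cure of 95.5%. The loss step is consistent: 235 / 0.95 = 247.4, so 248, rounded up to 250.

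**Step 2. Arm sizes under each reading.**

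| Reading | Enrolled (test:comparator) | Evaluable after 5% loss |
|---|---|---|
| 1:1, as in Sample size calculation | 250:250 | 235:235 (figure required) |
| 2:1 throughout | 333:167 | 317:158 |
| First 300 at 2:1 (200:100), last 200 at 1:1 | 300:200 | 285:190 |
| First 300 at 2:1, total forced to 250:250 | 200:100, then 50:150 | – |

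At 2:1 throughout the comparator has 158 evaluable patients, 77 fewer than 235, or about a third. The fourth reading needs 1:3 in the last 200, which appears nowhere and which blocks of 9 at 6:3 cannot give.

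**Step 3. Power.** Power = Φ(0.05 / SE − z_alpha), with SE = √[0.0475 × (1/n_test + 1/n_comparator)].

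- 235:235: SE = 0.02011; Φ(2.487 − 1.960) = 70.1%.
- 317:158: SE = 0.02122; Φ(2.356 − 1.960) = 65.4%.
- 285:190: SE = 0.02041; Φ(2.449 − 1.960) = 68.8%.

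At one-sided 0.05 the same three splits give 80.0%, 76.1% and 78.9%.

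From 80% down to 65.4% is 14.6 points. Of these, 70.1 − 65.4 = 4.7 come from the split and 9.9 from the mismatch in alpha.

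**Step 4. Exact power at one-sided 0.025**, summing binomial probabilities with 95% cure in both arms.

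| Interval | 235:235 | 317:158 | Change at 2:1 |
|---|---|---|---|
| Wald | 70.6% | 68.4% | −2.2 points |
| Newcombe | 66.2% | 71.6% | +5.4 points |

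The protocol does not name the interval method, so the cost of the split lies between about 5 points and none.

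**Step 5. Size needed at 2:1 for 80% power.** Comparator n = (z_alpha + z_power)² × 1.5 × 0.0475 / 0.0025.

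- One-sided 0.025: 223.7, so 224 + 448 = 672 evaluable (708 enrolled with 5% loss).
- One-sided 0.05: 176.2, so 177 + 354 = 531 evaluable (560 enrolled).

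Both exceed 500.

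**Step 6. Illustration of a period effect, under assumptions.** Take 200:100 then 50:150, equal drugs, and cure falling from 96% to 92% in both arms.

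- Test: (200 × 0.96 + 50 × 0.92) / 250 = 0.952.
- Comparator: (100 × 0.96 + 150 × 0.92) / 250 = 0.936.
- Crude difference: +1.6 points in favour of the test drug, with no true difference.

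**The case against.** The inconsistency itself is hard to dispute, but its consequences are easily overstated.

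A reader might set 65% beside the stated 80% and blame the whole gap on allocation. The figures do not support that: a true 235:235 already has only about 70% power at the stated alpha. By exact Wald the split costs about 2 points, and by Newcombe 2:1 has the higher power. The comparator arm is a third smaller, but the test arm is correspondingly larger and the total is unchanged. This objection stands in full.

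A reader might also infer that the primary comparison is confounded by enrolment period. That needs two things the documents do not contain: a change of ratio after the first 300 patients, and a change in cure over time. The 50:150 phase is only one way of reconciling the sections, and under constant 2:1 there is no such confounding. The compatibility statement concerns the data of the first 300 patients and does not expressly mention allocation. The 4-point drift is my assumption. This objection also stands, so the period effect remains a conditional point.

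Finally, a fixed block size named in an open-label protocol might be read as making allocation predictable. That is a general preference, separate from this contradiction. The protocol provides an externally generated list and sealed envelopes under a standard operating procedure, and nothing in it puts a size on the risk.

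**Conclusion.** The contradiction holds. The planned equal arms cannot come from the described list, the list fits the 2:1 parent design, and nothing in the protocol reconciles the two. That 2:1 applies at Kilifi is an inference, because no ratio is stated there.

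If it applies throughout, the comparator has about 158 evaluable patients rather than 235, and power is about 65% at one-sided 0.025. This rests on 95% cure in both arms, 5% loss and the normal approximation. Allocation accounts for about 5 points of the shortfall from 80%, and less or none by exact methods. The larger part comes from the separate mismatch between 235 and the stated alpha, so correcting the ratio alone will not restore 80%. Bias by enrolment period is possible only if the ratio changes between periods and cure drifts as well.

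**What to change.** - In Randomisation, state the allocation ratio for the first 300 patients and for the extra 200, and use block sizes that fit each ratio.
- In Sample size calculation, correct the arm sizes to that ratio and restate the power for the actual split, the alpha used in the analysis and an explicit test-arm cure ratio. If 2:1 is kept and 80% power is wanted, 500 patients are too few under either alpha (Step 5).
- Only if the ratio differs between the two enrolment periods, estimate the primary difference stratified by period, for example with a Mantel-Haenszel risk difference.

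The cost is wording, a matching randomisation list and, if enrolment stays at 500 and alpha at one-sided 0.025, a stated power clearly below 80%. The ratio and the list need to be settled before enrolment, because allocation cannot be repaired afterwards.

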### Stopping rule/discontinuation criteria

No further patients will be enrolled into the study until the Principal Investigator (PI), clinical monitor and the sponsor have evaluated details of any serious adverse event.

The study will be stopped if the serious adverse event is classified as a serious adverse reaction to the study drug as assessed by the PI, monitor and sponsors in accordance with the definition of Good Clinical Practice/International Conference on Harmonisation guidelines.

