### Exclusion criteria

1. Participation in any investigational drug study during the previous 30 days.
2. Known hypersensitivity to the study drugs.
3. Severe malaria.
4. Danger signs: not able to drink or breast-feed, vomiting (>twice in 24 hours), recent history of convulsions (>1 in 24h), unconscious state, unable to sit or stand.
5. ECG abnormality that requires urgent management.
6. Presence of intercurrent illness or any condition which in the judgment of the investigator would place the subject at undue risk or interfere with the results of the study.
7. Severe malnutrition (defined as weight for height <70% of the median NCHS/WHO reference).

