# INVESTIGATIONAL PRODUCTS & CONCOMITANT MEDICATIONS AND NON-DRUG THERAPIES

## Investigational products

### Study medication and dosages

The study medications (Clinical Trial Material (CTM)) to be evaluated in this study will be prepared and provided by Sigma-Tau i.f.r. S.p.A., Pomezia (Rome), Italy.

The stability of the products used in the study will be determined in advance to assure suitability for use throughout the study. The results of these analyses will be included in the Trial Master File.

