### Masking of treatment allocation

Because of the clear differences in form and colour of the two drug preparations, blinding of the treatment will not be possible at the point of administration. The use of the double-dummy technique with placebos for dihydroartemisinin-piperaquine and for artemether-lumefantrine would result into the administration of an excessive number of tablets per patient. However, all laboratory analyses including PCR will be performed by staff that will be unaware of the treatment allocation.

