## Data Safety Monitoring Board (DSMB)

An independent Data Safety Monitoring Board will review relevant efficacy data and all safety data.

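### A single serious adverse reaction obliges the whole study to stop, with no discretion, no route to resume and no step for the DSMB

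*Protocol*

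**What the plan says.** Protocol section 11.1.4 (Stopping rule/discontinuation criteria) has two steps.

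- **Pause.** After any SAE, "No further patients will be enrolled into the study until the Principal Investigator (PI), clinical monitor and the sponsor have evaluated details".
- **Stop.** "The study will be stopped if the serious adverse event is classified as a serious adverse reaction to the study drug", with the classification made "as assessed by the PI, monitor and sponsors in accordance with the definition of Good Clinical Practice/International Conference on Harmonisation guidelines".

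Section 15.4 sets up separate oversight: "An independent Data Safety Monitoring Board will review relevant efficacy data and all safety data". It describes no stopping or resumption step, and section 11.1.4 does not refer to it. Section 15.1 commits the investigators to telling the ethics committee about SAEs.

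The number of children at risk comes from section 10.4.2: "250 patients per treatment group (500 patients in total) will be enrolled in the Kilifi study".

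**The concern.** The pause is proportionate and is not in question. The difficulty is the second step. Once one SAE has been classified as a reaction, the consequence is fixed: nobody is given authority to weigh the event against the number of children already treated, the balance between arms or the severity of the reaction. No path leads back to recruitment.

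The protocol already provides a body suited to that judgement, an independent board that sees all safety data. Yet the classification that forces the stop is made by the investigator, monitor and sponsors, and the rule leaves the board nothing to decide.

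At stake is whether the trial answers its question. One isolated reaction, to either drug, would end it before non-inferiority to artemether-lumefantrine and the 90% cure criterion (section 9.1) could be tested.

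**Working it through.** **1. Does the text force a stop after one event?** The stop sentence refers to the same single SAE that triggered the pause. It gives no number of events, rate or comparison between arms. The wording is mandatory. It cannot fairly be read as a second pause, because the preceding sentence already supplies one and the section is headed as a stopping rule. The only resumption implied is of enrolment after an SAE that is *not* classed as a reaction.

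**2. Which drug counts?** Section 11.1.4 uses the singular. Other places bearing on the meaning are:

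| Place | Usage | Applies to |
| --- | --- | --- |
| 10.3.2 Exclusion criteria | "Known hypersensitivity to the study drugs" (plural) | both products |
| 10.7.1.2 Relationship of event to study drug | singular | every adverse event, so both arms |
| 12.2.3 Safety population | singular (study medication) | everyone given any dose, so both arms |
| 12.3.2.2 Safety and tolerability | singular | adverse event tables for the whole intention-to-treat population |

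The singular is therefore generic: whichever study drug the child received. A reaction to either treatment triggers the stop, and all 500 children are at risk of triggering it.

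**3. How likely is a stop?** The protocol gives no probability of stopping to reproduce and no serious adverse reaction rate, so the rate is an assumption.

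- Inputs: n = 500 (section 10.4.2), all assumed to be dosed; p = assumed chance per child of an SAE classified as a reaction, taken as equal in both arms and independent between children.
- Formula: P(at least one event) = 1 − (1 − p)^n.

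| Assumed p | Calculation | Chance of a stop |
| --- | --- | --- |
| 0.01% | 1 − 0.9999^500 | 0.0488 (about 5%) |
| 0.05% | 1 − 0.9995^500 | 0.2212 (about 22%) |
| 0.1% | 1 − 0.999^500 | 0.3936 (about 39%) |

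The rate at which a stop becomes as likely as not is p = 1 − 0.5^(1/500) = 0.001385, about 1 in 722 children.

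**4. Which rates are plausible?** The background section favours low ones: it reports only rare rash under large-scale piperaquine use. It also mentions rare type 1 hypersensitivity reactions to artemisinin drugs, and both arms contain one, so the trigger is not purely hypothetical. Nothing in the protocol narrows the rate further.

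**The case against.** The best defence is that a very conservative rule is a legitimate choice for young children receiving a new formulation whose bioavailability is only expected to match that of the old one (section 6). Judgement is also exercised before the stop, in the causality classification. DSMB procedures commonly sit in a charter that is not shown here. The size of the risk is wholly assumed, and it stays below one half at every rate tabulated.

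Much of this stands, and it is why the point is minor. It does not remove the point. The protocol itself fixes the outcome, so a charter allowing continuation would contradict it. The prior judgement concerns causality only, not whether the trial should go on. Caution is equally served by continued suspension, since the board may still recommend stopping, and section 10.8.2 already lets the investigator withdraw an individual child for safety.

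Four stronger readings are tempting but unsupported:

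- *A reader cannot tell whether the comparator counts.* The singular alone suggests this, but the generic usage in sections 10.7.1.2, 12.2.3 and 12.3.2.2 settles it in favour of both drugs.
- *The DSMB is shut out.* Section 11.1.4 is silent on the board and does not bar its advice. The fault is the missing link.
- *Unblinded assessors bias the result.* Section 11.1.2 does say that "blinding of the treatment will not be possible at the point of administration", but nothing shows that the stopping rule distorts the treatment estimate.
- *The trial will probably stop early.* With 500 exposed, that needs a rate above about 1 in 722, which the documents do not establish.

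**Conclusion.** The point holds as a badly fixed rule, of minor severity. Section 11.1.4 requires the study to stop once one SAE is classified by the investigator, monitor and sponsors as a serious adverse reaction to either treatment. It allows no discretion, states no route to resume and makes no connection to the independent board of section 15.4.

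That conclusion rests on the text and does not depend on the probabilities, which are illustrations under assumed rates, equal in both arms, with all 500 children exposed. The consequence is conditional on such an event occurring. No effect on the treatment estimate, the type I error or the endpoint definitions is claimed.

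**What to change.** Keep the enrolment pause after any SAE exactly as it is. Replace the stop sentence in section 11.1.4 with:

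> *If the serious adverse event is classified as a serious adverse reaction to either study drug, enrolment remains suspended and the event is sent promptly to the DSMB; the decision to continue, modify or stop the study is taken on the DSMB's recommendation.*

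Naming either study drug also makes the intended reading explicit. Add a matching entry to the DSMB procedures, where a target time for the review can be set.

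The cost is one sentence and that entry, since the board already exists. The downside is a short delay while it reviews the event, during which no new child is enrolled.

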### Accountability procedures for the investigational drugs

The PI will ensure that all clinical supplies are properly received, stored and documented. Only authorized dispensing staff will handle the study medication. These dispensing staff will account for all used and unused drug supplies. A Drug Accountability Log will be recorded in the investigator’s file (entries consisting of subject number, initials, date, time, number of tablets; dated and initialised by authorised members of the study team). The remaining medication will be kept in the original blister packages and stored for clinical monitoring and drug accounting purposes.

All investigational products will be used only in accordance with the protocol: any discrepancy between drugs received, used and returned will need to be explained.

## Concomitant medication and non-drug therapies

### Permitted Medications

All concomitant medications taken during the study will be recorded in the CRF with indication, dose information, and dates of administration. All subjects may be given paracetamol as an analgesic during the study, at the discretion of the treating physician. Antibiotics without known antimalarial activity, e.g. penicillin, cephalosporins and aminoglycosides, can be prescribed.

### Prohibited Medications

Any antimalarial, or antibiotic with antimalarial activity (erythromycin and other macrolides, co-trimoxazole and other sulphonamides, any tetracycline (including doxycycline, and quinolones). Intake of such drugs will lead to the withdrawal of the patient from the study and classification as treatment failure in the intention-to-treat population.

## Treatment failure

A subject will be considered a treatment failure if they experience either early or late treatment failure based on the following definitions.

